## Abstract

**Background:**

Accidental falls, especially for the elderly, are a major health issue. Balance disorders are one of their main causes. Vestibular rehabilitation (VR) has proven to be useful in improving balance of elderly patients with instability. Its major handicap is probably its cost, which has prevented its generalisation. So, we have designed a clinical trial with posturographic VR, to assess the optimum number of sessions necessary for a substantial improvement and to compare computerised dynamic posturography (CDP) (visual feedback) and mobile posturography (vibrotactile feedback).

**Methods:**

*Design*: randomized controlled trial. It is an experimental study, single-center, open, randomized (balanced blocks of patients) in four branches in parallel, in 220 elderly patients with high risk of falls; follow-up period: twelve months. *Setting*: Department of Otorhinolaryngology of a tertiary referral hospital. *Participants*: people over 65 years, fulfilling two or more of the following requirements: a) at least one fall in the last twelve months. b) take at least 16 s or require some support in perform the “timed up and go” test. c) a percentage of average balance in the sensory organization test (SOT) of the CDP < 68%. d) at least one fall in any of the conditions in SOT-CDP. e) a score in Vertiguard’s gSBDT > 60%. *Intervention*: Four differents protocols of vestibular rehabilitation (randomization of the patients). *Main outcome measure*: The percentage of average balance in the SOT-CDP. *Secondary measures*: time and supports in the “timed up and go” test, scores of the CDP and Vertiguard, and rate of falls.

**Discussion:**

Posturographic VR has been proven to be useful for improving balance and reducing the number of falls among the aged. However, its elevated cost has limited its use. It is possible to implement two strategies that improve the cost-benefit of posturography. The first involves optimising the number of rehabilitation sessions; the second is based on the use of cheaper posturography systems.

**Trial registration:**

ClinicalTrials.gov identifier: NCT03034655. Registered on 25 January 2017.

## Background

Accidental falls, especially for the elderly, are a major health problem in Western society [1, 2]. Approximately one-third of those over 65 suffer at least one fall per year; among those over the age of 85, this rises to approximately half. Furthermore, those who fall will often fall regularly (several times per year).

The repercussions of these falls in terms of morbimortality are serious, particularly because of associated bone fractures. Especially grave are hip fractures. Even if bone fractures do not result from the fall, the psychological consequences of falls seriously affect the quality of life of those affected. People who have suffered a fall tend to fear that this will happen again, and thus to reduce their physical activity. This, in turn, increases the chances of new falls and increases levels of fear, in a vicious circle that often leads to isolation and increasing dependency on carers [3].

In addition to these clinical and psychological consequences, the economic repercussions of the problem are also serious. The direct healthcare expenditure of these falls is very high, and the indirect cost of the recovery process and the monitoring thereafter is also very significant; there is the cost of increased care, and of adapting the home to the person’s new needs (ramps for wheelchairs, lifts and/or elevating platforms, handles in bathrooms) as well as the expense of other mobility equipment (walking supports, crutches, walking frames, etc.).

Many factors contribute to the risk of falls [4], including problems in the central nervous system that affect coordination and motion, balance disorders of different origins (vestibular, locomotor, visual, etc.), and advanced age [5] and age-related sensorial impairments [6, 7]. Several strategies can minimise risk [8, 9]; it is important to identify those in gravest danger of falling, in order to implement the necessary precautionary measures and to prevent (or at least to slow down) the age-related causes of falls using training and rehabilitation.

Vestibular rehabilitation has proven to be useful in improving the balance of elderly patients with instability [10–12]. Several protocols for vestibular rehabilitation exist (home exercises, Tai-Chi [13], optokinetic stimulus, rotating chairs, dynamic posturography exercises, etc.). Dynamic computerized posturography has proven to be especially useful for elderly patients, because it not only improves the stabilisation of the centre of gravity (where sensorial stimuli are absent or altered), but also improves the stability levels of the patient (and thus reduces the risk of falling) [14, 15]. Its major handicap is probably its cost, which has prevented its dissemination and generalisation.

Two possible solutions are presented here, which may serve to reduce this cost. One of these is optimising and reducing the number of vestibular rehabilitation sessions. This strategy has already proven useful for patients whose lack of balance is caused by reasons other than age [16]. The other option is using cheaper posturography systems; for example, Vertiguard® (Vesticure GmbH, Germany), which allows for the analysis of the motion of the centre of gravity in the course of daily activities, in both static and walking patients, as well as vibrotactile stimulation feedback-assisted rehabilitation [17]. This system has proven to be effective with different pathologies [18, 19], but no extensive and systematic studies have yet been undertaken that compare it with dynamic posturography in the treatment of age-related balance deficits.

For this reason, we suggest that it would be fruitful to undertake a study of vestibular rehabilitation in unstable aged patients, which will permit a double assessment. This study will:Evaluate the optimum number of sessions necessary for a substantial improvement (five vs ten);Compare computerised dynamic posturography (visual feedback) and mobile posturography (vibrotactile feedback).

This study was funded by the project PI1500329, integrated into the Spanish State Plan for R + D + I and funded by the ISCIII-Subdirección general de Evaluación y Fomento de la Investigación and the Fondo Europeo de Desarrollo regional (FEDER).

## Methods and design

### Aim of the study

The primary objective is to evaluate the effectiveness of a mobile posturographic system with vibrotactile neurofeedback to improve balance in elderly patients. Each subject was assessed immediately after the rehabilitation.

The secondary objectives are:To verify that improvements in balance are maintained in the medium term (six to twelve months).To consider whether this improvement in balance results in a reduction in the number of falls suffered by the elderly.To assess whether the reduction in the number of vestibular rehabilitation sessions (five) leads to similar results (an improvement in balance and a reduction in the number of falls) to those obtained after ten sessions. Both rehabilitation systems are compared using computerised dynamic posturography and mobile posturographic with vibrotactile neurofeedback.

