### Design

This study is the continuation of a previous clinical trial conducted by our research group [14], comparing three different rehabilitation strategies (dynamic posturography exercises, optokinetic stimuli and exercises at home) and a control group, to improve balance in elderly. The design of both studies is similar.

This is a randomized controlled trial. It is an experimental study, single-centre, open-label and randomized (balanced blocks of patients) in four parallel branches. It involves 220 elderly patients (over 65 years of age) who are at high risk of falling, and a 12-month follow-up period will be applied.

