### Inclusion criteria

Persons at a high risk of falling shall meet at least two of the following requirements:They have fallen at least once over the last 12 months.They required more than 15 s to complete, or require support in, the TUG test.They obtained a mean CDP SOT balance score of < 68%.They have fallen at least once in the CDP SOT.They obtained a score in Vertiguard’s gSBDT of > 60%.

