### Randomisation and intervention

#### Visit 1

After the first screening visit, the patients who provided consent will be included in the study and randomised to one of the following study arms:A.**Intervention with dynamic computerized posturography exercises (ten sessions)**. The Smart Equitest program was used: 10 exercises per session, which were customized depending on each patient’s deficit (as observed in the earlier postural study), were undertaken. The exercises involve visual biofeedback together with sensitive, real-time monitoring of movement. For some exercises, patients must maintain their centre of gravity (COG) over the base of support, while for others the COG must be moved to a series of targets. In addition, the support surface and/or visual surround may also move in response to the patient’s own movement. The exercise difficulty was progressively increased throughout the rehabilitation sessions by increasing the LOS, the transition rate or the movement of the posturography platform. The duration of each session was approximately 15 min. The distribution of sessions was one per day and five per week (two weeks)B.**Intervention with dynamic computerized posturography exercises (five sessions)**. Same as Group A, except for the number of sessions (5) and their distribution (one session on alternate days, for two weeks).C.**Intervention with mobile posturography (Vertiguard) exercises (ten sessions)**. As many as six tasks were set, and the most prominent deviations from normative control values were included in the training programme. Individual feedback was stored in the device for each patient based on body sway analysis. Training was performed using the training function of Vertiguard-RT device. This neurofeedback system contains a battery-driven main unit which is fixed on a belt at the centre of the body mass (hip) and one vibration stimulator on the front, back, left and right side, respectively. Vibration stimulators are mounted on the same belt as the main unit. They were adjusted by sliding them over the belt to the correct position for the individual patient. The main unit continuously determines the Coriolis force during body movements (pitch and roll) using inbuilt gyroscopes and compares those values with individual pre-set thresholds for stimulator activation in specific directions.Training was performed daily under the supervision of a physician over 2 weeks (over 10 sessions and the weekend was excluded). A training session consisted of 5 repetitions of six selected training tasks as described above (each repetition lasted 20 s or until the movement was finished). The patient received a vibrotactile feedback signal during training for those directions when a body sway higher than pre-set thresholds was noted. Vibration was reinforced with increasing sway: the more it exceeded the pre-set values, the stronger the vibration was at the corresponding site.No vibrotactile feedback was applied if the patient’s sway was below pre-set thresholds. The exercise difficulty progressively increased throughout the rehabilitation sessions by pressing the sensitivity buttons (up/down) on the main unit. During this procedure, the individual pre-set thresholds were similarly decreased for all sway directions of the specific training conditions until the patient perceived a vibration while performing the training task.D.**Intervention with mobile device Vertiguard exercises (five sessions)**. Same as Group C, except for the number of sessions (5) and their distribution (one session on alternate days, for two weeks).

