### Data collection and ethics

The balance study undertaken in the first visit (**baseline record**) is repeated, with all the tests (questionnaires, TUG test, CDP SOT, CDP limits of stability and Vertiguard record) three more times:

● Visit 2.- Immediately after completion of VR.

● Visit 3.- Six months after VR.

● Visit 4.- Twelve months after VR.

The data will be collected in a specially designed database. There will be periodic data quality controls. The PI will monitor the study and ensure that the data are authentic, accurate and complete, and that the subjects’ safety and rights are protected.

The protocol has been approved by the Independent Ethics Committee of Galicia (protocol 2014/411).

The study will be conducted according to ICH Good Clinical Practices (GCP), the Declaration of Helsinki and Law 14/2007, of 3 July, on Biomedical Research.

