#### Bivariate analysis

We will provide the differences (95% CI) in the balance test assessments between baseline and end of intervention, and 6 months and 12 months post-intervention. These measures will be compared between groups by ANOVA or the Kruskall-Wallis test if normality is not assumed.

The Chi-squared test or Fisher’s exact test, depending on the conditions, will be used to analyse the number of falls occurring from 12 months prior to inclusion and 12 months post-intervention.

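### The primary objective claims effectiveness for the mobile system with no comparator, but every arm is active, so only relative questions can be answered and change from baseline cannot stand in for a control

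*Protocol article*

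**What the plan says.** Under Aim of the study the protocol article states: "The primary objective is to evaluate the effectiveness of a mobile posturographic system with vibrotactile neurofeedback to improve balance in elderly patients". The next sentence fixes the time point: "Each subject was assessed immediately after the rehabilitation". No comparator is named. Comparison of the two systems appears only at the end of the secondary objectives. The Abstract and Background instead give the purpose as finding the optimum number of sessions (five or ten, in the Background) and comparing CDP with mobile posturography.

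The Design section describes the trial as "single-centre, open-label and randomized (balanced blocks of patients) in four parallel branches". Under Randomisation and intervention, arms A and B are CDP training (ten and five sessions), and arms C and D are Vertiguard training (ten and five). The control group mentioned under Design belongs to the group's previous trial, described as "comparing three different rehabilitation strategies (dynamic posturography exercises, optokinetic stimuli and exercises at home) and a control group".

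The primary endpoint is the SOT average. Entry requires any two of five criteria. One is "They obtained a mean CDP SOT balance score of < 68" per cent, and another is a fall during the same SOT. These tests are done at pre-screening visit 0, and Visit 1 describes only randomisation and intervention. Data collection and ethics refers to "The balance study undertaken in the first visit", calls it the baseline record, and has it repeated three times after rehabilitation. The analytical plan also ties baseline characteristics to visit 0.

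The sample size rests on a within-patient change from 64 to 73 or 74. Bivariate analysis begins: "We will provide the differences (95% CI) in the balance test assessments between baseline and end of intervention". It then plans an ANOVA or Kruskal-Wallis comparison between groups. Multivariate analysis plans a repeated-measures model of improvement from baseline, with treatment as a fixed factor. No margin is stated.

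**The concern.** A claim that a device is effective needs something to be effective against. With four active arms, randomisation supports statements about one system or session number relative to another. It gives no estimate of what would have happened without rehabilitation. The quantity closest to the stated objective is then change from baseline in the mobile arms, and that has no concurrent control.

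That change is also open to bias from selection. The baseline SOT is the measurement that helped to qualify the patient, and one poor SOT can meet two of the five criteria and so suffice for entry. A score selected for being low tends to be higher on retest even without treatment. Familiarity with the test and non-specific effects of two weeks of supervised attendance may add to this, although the document gives no figure for either.

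At stake is what the trial may conclude. A gain from baseline in the mobile arms could be read as meeting the primary objective when it does not isolate the device's effect.

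**Working it through.** **1. The plan's own figures.** The stated change is 10 points. The listed values give 73 − 64 = 9 immediately after rehabilitation and 74 − 64 = 10 at 12 months. No SD or sidedness is given, so 53 per arm can only be solved backwards. For a two-sided 5% test of two means with 80% power, n = 2 × SD² × (1.96 + 0.84)² / delta².
- Delta 10, SD 18.35: 2 × 336.7 × 7.85 / 100 = 52.9, rounded up to 53.
- Delta 9, SD 16.5: 2 × 272.25 × 7.85 / 81 = 52.8, rounded up to 53.

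The implied SD is therefore about 16.5 to 18.35 (an assumption). The only delta offered is a change from baseline, not a difference between arms or against no treatment.

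**2. Regression to the mean.** The document gives no source mean, SD or test-retest correlation r, so all of these are assumed. If entry were by SOT below 68 alone, the expected change without treatment would be (1 − r) × (source mean − mean of those selected).
- Source mean 64, SD 8, selected mean 59.9, r = 0.9: 0.1 × 4.1 = 0.4 points.
- Source mean 68, SD 12, selected mean 58.4, r = 0.6: 0.4 × 9.6 = 3.8 points.
- Source mean 72, SD 15, selected mean 57.4, r = 0.5: 0.5 × 14.6 = 7.3 points.

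Entry is not by SOT alone. A simulation of one version of the two-of-five rule (source mean 68 or 72, SD 12, r from 0.9 to 0.6) gave about 0.4 to 1.7 points. Against the 9-point change that is 0.4/9 = 4% to 1.7/9 = 19%. The result also depends on how often the other criteria are met. The fewer patients who qualify by falls, timed up and go or gSBDT, the closer it moves to the SOT-only figures.

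**3. What a small shift does to an uncontrolled test.** For a spurious shift d, the chance of significance in a two-sided 5% before-after test depends on d / (SD of change / √n). With an assumed SD of change from 15 down to 8:

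| Shift | n = 53 (one arm) | n = 110 (both mobile arms) |
|---|---|---|
| 2 points | 0.16 to 0.44 | 0.29 to 0.75 |
| 3 points | 0.31 to 0.78 | 0.55 to 0.98 |

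The nominal rate is 0.05.

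**4. Could the comparison with CDP carry the claim?** Only indirectly, through a non-inferiority margin. With two arms pooled, n = 106 per group. At one-sided 2.5%, 80% power and a true difference of 0, the margin supported is 2.80 × SD × √(2/106).
- SD 16.5: 2.80 × 16.5 × 0.1374 = 6.3 points.
- SD 18.35: 2.80 × 18.35 × 0.1374 = 7.1 points.

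Each is about 70% of the change from which its SD was solved (6.3/9 and 7.1/10). Baseline adjustment would reduce the margin by an amount the document does not allow one to state.

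**The case against.** The strongest reply is that this is a randomised trial against an active comparator that the Background calls proven. Between-group comparisons are planned in the Bivariate and Multivariate sections, and the aims themselves say that the systems are compared. All of that stands. A reader might infer that the primary objective can be judged only by before-after change, or that the trial can say nothing useful about the mobile system. The documents do not support either: the relative comparison is planned and valid. Nor does any section make a within-arm test the criterion of success. Differences from baseline are only to be reported.

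The reply does not repair the objective as worded. A non-significant ANOVA across four active arms does not show that any of them works, and no margin links the mobile system to the accepted benefit of CDP.

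A second tempting reading is that regression to the mean explains a large part of the gain. Taking the protocol's 64 with an assumed source mean of 70 to 74 and r of 0.8 to 0.6 gives 0.2 × 6 = 1.2 to 0.4 × 10 = 4.0 points, or 13% to 44% of 9. That treats the whole gap as selection on SOT, whereas any two of five criteria suffice. The 64 also comes from earlier studies whose selection is not shown. Patients drawn from a neurotology unit could have a source mean near 64, which would make this figure close to zero.

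A further reply is that a statistical analysis plan may settle the matter. The objective and the arms are both fully stated here, so the mismatch lies in the text itself.

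**Conclusion.** The point holds as a mismatch between the stated primary objective and the design. The objective has no comparator, all arms are active, and the abstract and background lead with questions that the design can answer. Change from baseline cannot by itself establish effectiveness, because no arm removes regression to the mean, retest learning or non-specific effects.

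The structural part is certain from the text. The size is not. Regression to the mean of about 0.4 to 1.7 points rests on assumed source mean, SD, correlation and criterion frequencies, and is a minor to moderate share of 9 to 10 points. Learning on retest is a possibility, not a documented effect. The missing concurrent control is therefore the main issue, and selection on the SOT is secondary.

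**What to change.** Reword the primary objective, identically in the aims, abstract and background, as the randomised comparison of the SOT average immediately after rehabilitation, mobile (C and D) versus CDP (A and B), adjusted for baseline SOT and reported as a difference with 95% CI. Keep five versus ten sessions as a secondary comparison. Selection on the baseline SOT then affects both sides alike. One caveat belongs in the text: arms A and B train on the Smart Equitest system, which also measures the endpoint, so familiarity with it may differ between systems.

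Label within-arm changes as descriptive, and state that they may include regression to the mean and retest effects.

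If a claim of being not worse is wanted, set and justify a margin in advance, and state that the present size supports only about 6.3 to 7.1 points before baseline adjustment, on the implied SD.

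Cost: for the estimate with its interval, rewording only, with no added patients or visits. A tighter non-inferiority margin might need more patients. The trial gives up a stand-alone claim that the mobile device is effective. Keeping that claim would require an untreated or sham arm. A fresh pre-treatment SOT would reduce regression to the mean but would not replace a control.

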### Design

This study is the continuation of a previous clinical trial conducted by our research group [14], comparing three different rehabilitation strategies (dynamic posturography exercises, optokinetic stimuli and exercises at home) and a control group, to improve balance in elderly. The design of both studies is similar.

This is a randomized controlled trial. It is an experimental study, single-centre, open-label and randomized (balanced blocks of patients) in four parallel branches. It involves 220 elderly patients (over 65 years of age) who are at high risk of falling, and a 12-month follow-up period will be applied.

### Study duration

The study period is 36 months.

### Study subjects

**Study population**: people over 65 years of age.

**Target population**: people over 65 years at a high risk of falling, from the Santiago de Compostela area.

Subjects > 65 years of both genders, at a high risk of falling (according to criteria to be described), will be included. These people will be selected from a larger population categorised according to one of the following characteristics:Patients > 65 years who visit the Neurotology Unit with balance disorders, in whom causes other than advanced age have been ruled out.Patients with no subjective balance disorder, who have not been seen for this reason, who agree to undergo the examination protocol; for these patients, it must be verified that they meet the established fall risk criteria.

**Pre-screening visit 0**: This involves a complete balance examination and interview that enables us to select individuals with balance disorders who are at a high risk of falling and are thus candidates for inclusion in the study.

This visit includes the following:Questionnaires that measure disability caused by imbalance and risk of falling. Such questionnaires include:Direct questions about the number of falls over the last 12 months.Dizziness Handicap Inventory (DHI), validated in Spanish [20], and a shortened version of the Falls Efficacy Scale-International (FES-I) to assess fear of falling (Short FES-I) [21], which evaluates the fear of falling while performing seven everyday activities. An explanation of scores of these questionnaires has been previously published [14].b)Modified “timed up and go” (TUG) test [22, 23]: the subject, seated, must stand up unaided, walk 3 m, turn around and sit down again. The time needed, the number of steps taken and the need for support are determined.c)Computerised dynamic posturography (CDP) sensory organisation test (SOT) and limits of stability (LOS); we used the Neurocom® Smart Equitest platform. Performing of SOT and LOS has been previously published [14].d)Studying the balance record using the mobile Vertiguard® system: 13 tasks are performed; their analysis represents the geriatric Standard Balance Deficit Test (gSBDT):Standing still (SS), eyes open, normal surface (NS).SS, eyes closed, NS.8 steps in tandem, eyes open, NS.SS, eyes open, foam surface (FS).SS, eyes closed, FS.8 steps in tandem, eyes open, FS.Walk 3 m, eyes open.Walk 3 m, eyes open, turning the head from side to side.Walk 3 m, eyes open, moving the head up and down.Walk 3 m, eyes closed.Walk over 4 barriers (height: 26 cm; distance between barriers: 1 m).Sit on a chair.Get up from a chair.

The subject’s eligibility will be verified upon completion of these tests. If he/she meets the inclusion criteria and none of the exclusion criteria apply, then the investigator will provide him/her with a detailed, systematic explanation of the study’s objectives and what participation involves, inviting him/her to join. The subject will be given the approved information sheet in order to obtain his/her written informed consent.

